## Abstract

**Background:**

Mental illness is a significant and growing problem in Canadian healthcare organizations, leading to tremendous personal, social and financial costs for individuals, their colleagues, their employers and their patients. Early and appropriate intervention is needed, but unfortunately, few workers get the help that they need in a timely way due to barriers related to poor mental health literacy, stigma, and inadequate access to mental health services. Workplace education and training is one promising approach to early identification and support for workers who are struggling. Little is known, however, about what approach is most effective, particularly in the context of healthcare work. The purpose of this study is to compare the impact of a customized, contact-based education approach with standard mental health literacy training on the mental health knowledge, stigmatized beliefs and help-seeking/help-outreach behaviors of healthcare employees.

**Methods/Design:**

A multi-centre, randomized, two-group parallel group trial design will be adopted. Two hundred healthcare employees will be randomly assigned to one of two educational interventions: Beyond Silence, a peer-led program customized to the healthcare workplace, and Mental Health First Aid, a standardized literacy based training program. Pre, post and 3-month follow-up surveys will track changes in knowledge (mental health literacy), attitudes towards mental illness, and help-seeking/help-outreach behavior. An intent-to-treat, repeated measures analysis will be conducted to compare changes in the two groups over time in terms of the primary outcome of behavior change. Linear regression modeling will be used to explore the extent to which knowledge, and attitudes predict behavior change. Qualitative interviews with participants and leaders will also be conducted to examine process and implementation of the programs.

**Discussion:**

This is one of the first experimental studies to compare outcomes of standard mental health literacy training to an intervention with an added anti-stigma component (using best-practices of contact-based education). Study findings will inform recommendations for designing workplace mental health education to promote early intervention for employees with mental health issues in the context of healthcare work.

**Trial registration:**

May 2014 - ClinicalTrials.gov: NCT02158871.

## Background

Mental illness in the workplace costs the Canadian economy an estimated $21 billion a year in reduced labour force participation [1]. It is associated with more lost work days than any other chronic condition, and the cost of mental health leave is, on average, double the cost of a leave for a physical illness [2]. Mental illness at work is a particularly costly issue for healthcare organizations. Healthcare workers in Ontario report high levels of workplace stress, and have a higher risk of mental health problems than any other occupational group [3,4]. Healthcare workers are more likely to miss work due to illness or disability and tend to be absent for significantly more days than workers in other sectors [5]. In addition, a high proportion of healthcare workers continue to work despite mental health problems [6]. Working despite mental illness, or presenteeism, can be more costly than absenteeism. Presenteeism can lead to poor work quality, interpersonal conflicts, and on the job errors and accidents [7]. Concerns about patient safety and quality of patient care have prompted calls for action to address this growing problem in healthcare organizations [8].

### Importance of early intervention for mental health issues

Despite the high prevalence and significant impact of mental health issues in healthcare work, the issues are often surrounded by secrecy and silence [9]. Many healthcare workers are reluctant to admit that they are ill, and do not seek help for their mental health problems when needed [6,10]. There is often a long lag time between the onset of symptoms and seeking treatment [11,12].

When a worker is struggling, managers and co-workers might not say or do anything because they do not recognize the signs of mental illness, they do not know how to respond, and/or they may judge the worker as “bad” rather than “ill” [13,14]. In healthcare, there can be a discourse of professional competence where it is not acceptable to admit the need for help [9,15]. Consequently, many workers do not get the help or support that they need and mental health issues can escalate to the point of crisis before they are addressed. Early intervention is critical to prevent the personal, social and financial costs of untreated mental health issues at work [16].

Early intervention, as defined in this study, is facilitated by knowledge, attitudes and behaviors that facilitate timely, effective and appropriate support for workers with emerging signs and symptoms of mental health problems or disorders [17]. Support may involve a range of options, from counseling and/or medication from a healthcare provider to connection with an Employee Assistance program or a self-help group. The conceptual model of early intervention guiding the project is outlined in Figure 1. Earlier intervention can be accomplished by augmenting two key health access behaviors; a) workers seeking help when they are struggling with their own mental health issues, and b) workers facilitating appropriate outreach to colleagues who are struggling in order to facilitate their help seeking behavior. Appropriate help seeking and outreach behaviors are considered together because they are the two primary mechanisms by which a worker receives the help that he/she needs, and they share common pathways [6]. Further, actions taken to facilitate early identification and intervention are mediated through reduction of stigma, improved mental health literacy and better attitudes towards professional treatment. This can have a dual effect on both help seeking and appropriate outreach to colleagues. Although the primary outcome of interest in this study is help seeking and outreach behavior, it should be noted that early intervention leads to more appropriate utilization of mental health services and faster recovery from mental health issues. The overall impact of greater efficiency, reduced absenteeism and sick leave, and increased productivity at work should provide economic advantages to both the worker and the employer [13]. Evaluation of these long-term outcomes is beyond the scope of this project, but will be the focus of subsequent research.

**Figure 1 Fig1:**
[figure not shown]
Conceptual Model of Early Intervention.

As outlined in the conceptual model, there are several key forces that may shape the nature and extent of early intervention for mental health problems. Mental health literacy, stigma, and beliefs about the value of seeking help are some of the key forces to consider [18]. Mental health literacy refers to the knowledge and skills required for recognition, management and/or prevention of mental disorders [19,20]. Literacy is a critical issue because many mental health problems are misunderstood or over-looked, therefore early identification is the first critical step in early intervention. Stigma, in the form of negative attitudes and stereotypical beliefs about mental illness is another key issue. Co-workers often judge workers with a mental illness and ostracize them rather than provide support [21]. These attitudes and beliefs contribute to fear of discrimination and are a substantial barrier to seeking help [22]. Another force that may shape behavior is one’s belief about the role and effectiveness of psychological treatment. If there is little faith in the value of a treatment approach, then a worker may not choose to pursue the treatment, and likewise a colleague may not recommend it to a co-worker who is struggling [18].

It should be noted that the model depicts a linear relationship between the key variables, however these relationships can be quite complex, and not always predictable. For example, mental health literacy training may or may not affect stigmatized beliefs; a decrease in stigma may not affect behavior; and experience in seeking help may reinforce or change beliefs about the value of a particular approach [23].

### Approaches to promote workplace mental health support

Many programs to promote early intervention for mental ill health at work are based on principles of mental health literacy training. Typically one or two sessions are scheduled to train stakeholders in the workplace about how to identify and respond to employees with mental health problems. Mental Health First Aid (MHFA) is one example of a well-established, standardized mental health literacy program that has been implemented and evaluated internationally in a variety of settings, including workplaces [24]. Outcomes of quasi-experimental and experimental studies of Mental Health First Aid training include improvement in recognition of mental disorders and their treatment, increased confidence in providing help for others, and increased helping behavior [25].

Although literacy initiatives show promise, they might not be sufficient in a healthcare environment. Many healthcare workers have reasonably high levels of mental health literacy. In fact, having a medical understanding of mental disorders appears to increase rather than decrease stigma and social distance, perhaps because the illness is perceived as fixed and chronic [26]. Stigma is reported to be quite high among healthcare workers [21]. Improvements in mental health literacy do not necessarily translate into reduced stigma or increased social inclusion [23]. In order to address the stigma associated with mental illness, contact-based education is recommended as a best practice approach [23]. Contact-based education (CBE) is a knowledge translation strategy that creates opportunities for positive interpersonal contact with someone who has personally experienced mental health issues [27]. Key ingredients for CBE include voluntary, positive, prolonged contact with a respected peer of equal status [28,29]. Positive interactions with a respected colleague who has personally experienced mental illness can disconfirm negative stereotypes, and the opportunities for active discussion can break down “us-them” barriers [28]. Evaluation studies of CBE with a range of student groups have reported positive outcomes, including a significant reduction in prejudice and social intolerance [27,30]. The impact on willingness to seek help, however, is not as clear [30].

Contact-based education led by a respected peer is a promising strategy to build literacy, promote positive attitudes, and reduce stigma, however, additional research is needed to systematically evaluate this approach and its impact on help-seeking/outreach behavior. A review of research on contact based education highlighted the potential of both retrospective and prospective contact, but also pointed to many methodological limitations in the literature and the need to examine the nature of contact [28]. There are no empirical evaluations of CBE in a workplace setting. One of the challenges is that CBE is more of a philosophy than a standardized approach to training. Many of the reports in the literature refer to single sessions involving personal story telling with a target audience, rather than the recommended principles of prolonged contact and active discussion [28]. This is a serious concern since definition and adherence to the active ingredients of intervention during its evaluation are fundamental to valid conclusions about its effectiveness. In this study, we propose to evaluate a workplace education program that integrates principles of CBE, including opportunities for ongoing active dialogue and discussion regarding the complex issues that shape the beliefs and behaviors of employees in healthcare organizations. According to principles of knowledge translation, a program is more likely to be effective if it is developed in partnership with stakeholders and tailored to the needs of the target audience [31]. In this study, we propose to evaluate a novel program called “Beyond Silence”, which was created to build on best practice principles of CBE as well as adult learning theory and knowledge translation in a healthcare setting. The plan is to compare its effectiveness to standard MHFA training that does not incorporate a contact-based education approach.

### Research questions

Is customized, contact-based education more effective than standard mental health literacy training in increasing the help-seeking/outreach behaviors of workers in a healthcare setting?What mediates the impact of the contact-based intervention?What is the effect of mental health literacy?What is the effect of attitudes towards coworkers with mental health issues?What is the effect of attitudes towards seeking professional treatment?What process issues need to be considered in implementing mental health education in a healthcare workplace?

## Methods/Design

A multi-centre, randomized, evaluator-blinded, two-group parallel design will be adopted, comparing the impact of the Beyond Silence (CBE) program with mental health literacy training. A parallel group design will be adopted where participants in both groups will receive 12 hours of group-based education, but the content, schedule and format will be different. The 1:1 randomization sequence will be generated off site (in Calgary) using the software Stata. Randomization will occur in four blocks of 26 and four blocks of 24, leading to n = 100 in each assignment group and exactly 12 or 13 participants in each assignment. The sequence will not be shared with the investigative team, who will instead determine each participant’s assignment using an interactive web-based system. Mental Health First Aid training (MHFA) will serve as the control group since its efficacy is already well established in the literature [32]. The “Beyond Silence” approach is novel, and based on best practice principles, but research is needed to determine whether it is effective. Help seeking/outreach behavior, mental health literacy, and mental health stigma will be assessed at 3 month intervals: at baseline, after completion of the program and at 3 months follow-up. The study protocol was registered in May 2014 on ClinicalTrials.gov (ID#: NCT02158871). Ethical approval was also obtained through the Hamilton Integrated Research Ethics board.

### Participants

The study will be conducted in two healthcare organizations in the same mid-sized urban center in southern Ontario. One is a large healthcare facility that employs approximately 10,000 full and part-time workers across five sites. The other organization is a mid-sized hospital with approximately 4000 employees across three main sites. Volunteer participants will be recruited through posters, staff newsletters, intranet sites, information sessions with program managers, and email follow-up. Inclusion criteria include: a) full, part-time or casual employment in any area of the organization, b) agreeable to being randomly assigned to either of the two programs, c) commitment to attending the 12 hours of mental health education outside of paid work time, and d) no prior training in either program. Screening will be completed by the project coordinator either via email or by telephone. Recruitment and random assignment to the two groups will continue over four intake periods in each organization, according the sample justification outlined below. Consent will be obtained from each participant prior to completion of the each online survey (pre, post and at 3-month follow-up), with a hard copy of the consent form provided at the start of the first in-person session.

The plan is to enroll 200 employees in total, with 100 participants in each group. In each of the four intake periods, we plan to include 24 to 26 participants, and will actively recruit to ensure sufficient numbers prior to randomization. Following randomization, an intent-to-treat analysis will be incorporated, including all study participants. Quantitative precision estimates suggest that this sample size is sufficient to detect any real and important benefit of CBE over literacy training on change in help-seeking behavior. Two RCT evaluations of MHFA (literacy) interventions among Australian healthcare workers found that 50% to 75% of workers reportedly offered help to a person with mental health problems, prior to the intervention [24,25]. Based on this, we expect an average of about 1–2 behaviors at baseline across the samples. To simplify, we approximate the precision to detect change in mean count from baseline to the 6 month follow-up using calculations for the linear mixed-effects model, but allowing for non-constant variance of the counts by assuming that the variance averaged over groups and occasions might be as high as 4. Also assuming high consistency of help-seeking within groups (test-retest correlation, 0.80), we have an 80% chance of finding a significant (p < .05) difference between the two groups in average change over 6 months of as little as 0.44 behaviors. That is, even if the real advantage of CBE over MHFA is very small (less than 1 new behavior, on average), we have a high probability of detecting it. The precision for estimating mediators such as changes in stigma scores is similarly high. Based on initial pilot data, there were significant increases in behavior over time therefore the projected sample size should be more than sufficient to detect change.

Compliance with the programs will be tracked through attendance rates, with 75% attendance considered to be good compliance. To minimize withdrawals or missing data, multiple strategies will be put in place to allow participants to respond (written, electronic) with incentives for survey completion and proactive follow-up by email and/or phone. Based on the level of engagement of pilot participants, minimal loss to follow-up is expected, but we will impute assuming random missing-ness if needed. The repeated measures mixed effects model accounts for missing data under a missing at random assumption, such that participants with a single missing follow-up survey do not need to be excluded from the data analysis.

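### The detectable difference of 0.44 behaviors needs an undeclared one-sided test or a contrast other than the one named; two-sided on the named contrast it is 0.50

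*Protocol article*

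**What the plan says.** All the inputs stand in one paragraph of the Participants section of the Protocol article.

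- **Size:** "The plan is to enroll 200 employees in total, with 100 participants in each group".
- **Contrast:** "we approximate the precision to detect change in mean count from baseline to the 6 month follow-up", using linear mixed-model calculations as a simplification.
- **Variance:** the authors allow that "the variance averaged over groups and occasions might be as high as 4".
- **Correlation:** "assuming high consistency of help-seeking within groups (test-retest correlation, 0.80").
- **Error rates:** "we have an 80% chance of finding a significant (p < .05) difference between the two groups".
- **Result:** a "difference between the two groups in average change over 6 months of as little as 0.44 behaviors".

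The paragraph then reads the result as high power "even if the real advantage of CBE over MHFA is very small (less than 1 new behavior, on average").

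The Data analysis section gives a directional hypothesis in favor of Beyond Silence. It rests the first research question on whether treatment group is significant in the mixed model, and mentions joint tests over all three surveys. Neither section says whether the 5% level is one- or two-sided.

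**The concern.** An undeclared 5% level for a difference between two groups is normally read as two-sided. Read that way, with the contrast the paragraph names, the inputs lead to a larger detectable difference than the one printed. The article's statement that the sample is large enough rests on this figure, and the comparator is an active program. A reader who takes 80% power at 0.44 at face value would credit the trial with more sensitivity than a two-sided test of that contrast gives, and could give a null result too much weight.

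**Working it through.** **Inputs (Participants section):** n = 100 per group; variance 4; correlation 0.80; power 80% (z = 0.842); level 5% (z = 1.960 two-sided, 1.645 one-sided). No allowance for loss or for training group is applied.

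**Standard error for the named contrast (baseline to 6 months)**

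- Var(change) = 2 × 4 × (1 − 0.80) = 1.6
- SE of the group difference = √(2 × 1.6 / 100) = 0.1789

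**Reproducing 0.44**

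- One-sided 5%, named contrast: (1.645 + 0.842) × 0.1789 = 0.445. At exactly 0.44, power is 79.2% and n for 80% power is 103 per group. This matches the printed figure.
- Two-sided 5%, mean of the two follow-ups minus baseline: variance = 4 × [(1 + 0.80)/2 + 1 − 2 × 0.80] = 1.2; SE = √(2 × 1.2 / 100) = 0.1549; detectable difference = (1.960 + 0.842) × 0.1549 = 0.434 (0.436 with the t distribution). Power at 0.44 is 81.1%. This is also close enough to match.

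**Two-sided 5% on the named contrast**

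- Detectable difference = (1.960 + 0.842) × 0.1789 = 0.501 (0.504 with the t distribution)
- Power at 0.44 = Φ(0.44/0.1789 − 1.960) = Φ(0.50) = 0.691
- n per group for 80% power at 0.44 = 2 × 1.6 × (1.960 + 0.842)² / 0.44² = 129.7, so 130

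**Other two-sided readings**

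| Reading | Variance | Detectable difference |
|---|---|---|
| Linear slope over three equally spaced surveys, scaled to 6 months | 1.6 | 0.501 |
| 6-month count adjusted for baseline | 4 × (1 − 0.80²) = 1.44 | 0.475 |
| Mean of follow-ups adjusted for baseline | 4 × (0.90 − 0.80²) = 1.04 | 0.404 |

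None of these three gives 0.44.

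**What would make 0.44 right, two-sided, on the named contrast**

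Var(change) would have to be (0.44/2.802)² × 100/2 = 1.233. That means a correlation of about 1 − 1.233/8 = 0.846 with variance 4, or a variance of about 1.233/0.4 = 3.08 with correlation 0.80.

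**The case against.** The strongest reply is that 0.44 is not a miscalculation. The article never says two-sided, its hypothesis is directional, and the one-sided calculation returns 0.445. This stands: a reader might infer that the figure cannot be derived from its inputs, and that would be wrong. It does not settle the matter, because a directional hypothesis does not declare a one-sided test and the text speaks only of a significant difference between groups.

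Second, the authors may have meant the average of both follow-ups against baseline, which reaches the figure two-sided. The wording about average change and the planned use of all three surveys leave room for this. The same paragraph, however, names the change to the 6-month survey. Nor is a joint test over three surveys the same as this average. If that joint test is a group-by-time test on 2 degrees of freedom under constant correlation 0.80 (an assumption), a difference of 0.44 at both follow-ups has noncentrality 0.44²/0.024 = 8.07 and power of about 72%. A difference growing linearly to 0.44 has noncentrality 0.44²/0.032 = 6.05 and power of about 59%. The two-follow-up reading remains possible, so it cannot be asserted that the authors used a one-sided test.

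Third, the variance of 4 is offered as an upper allowance. This also stands. A reader might call 69% the trial's true power, but it is the power at that variance, for one sidedness and one contrast. At a variance of about 3.08 the two-sided claim would hold.

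Fourth, a condensed article may leave sidedness to a fuller document. That excuses the omission. It does not excuse printing a figure whose usual reading, on the contrast stated beside it, gives a different number.

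**Conclusion.** The point holds in limited form. As a reader would ordinarily take it (two-sided 5%, baseline to 6 months, variance 4, correlation 0.80, 100 per group), the detectable difference is 0.50 rather than 0.44, and power at 0.44 is about 69% rather than 80%. The printed figure holds only under a one-sided level or a different contrast, and the article declares neither.

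The gap is 0.501 − 0.44 = 0.06 behaviors. A reader might conclude that the trial is too small and needs 130 per group. The documents do not support that: the authors' own benchmark is an advantage of less than one behavior, and 0.50 meets it. Whether such a difference deserves to be called very small is a matter of preference and no part of this finding.

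Both figures assume complete data and independent participants. The Interventions section has both programs taught in groups of about 12 to 13, so positive correlation within training groups, like any lost surveys, would raise the detectable difference. The article gives neither an intraclass correlation nor a loss rate, so no size is claimed for this. Severity: should be fixed.

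**What to change.** In the sample justification:

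1. State whether the 5% level is one- or two-sided, and which contrast 0.44 refers to.
2. If it is a two-sided test of baseline-to-6-month change, replace 0.44 with 0.50, or keep 0.44 and give power of about 69% at variance 4. If the mean of both follow-ups was meant, keep the figure and correct the description of the contrast. If a one-sided test was meant, declare it.
3. Add one sentence saying that the figure assumes complete data and independent participants, although training is delivered in groups of 12 to 13.

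The cost is wording only. Under the two-sided baseline-to-6-month reading the stated sensitivity becomes slightly less favorable. The sample size, design and analysis stay as they are.

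### The stated inputs give 80% power at 0.44 behaviors only under particular, unstated choices of contrast and sidedness, and the looser claim of high power below one behavior fails under 0.44

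*Protocol article*

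**What the plan says.** The sample justification is in the Protocol article, Methods/Design, Participants.

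- **Size:** "The plan is to enroll 200 employees in total, with 100 participants in each group".
- **Contrast:** change in the mean count from baseline to the 6-month follow-up, approximated with linear mixed-model calculations.
- **Variability:** the plan assumes that "the variance averaged over groups and occasions might be as high as 4", with a test-retest correlation of 0.80.
- **Result:** "we have an 80% chance of finding a significant" difference "in average change over 6 months of as little as 0.44 behaviors". The significance level is given as p < .05 without saying whether the test is one- or two-sided.
- **Restatement:** the next sentence says "even if the real advantage of CBE over MHFA is very small (less than 1 new behavior, on average), we have a high probability" (the probability meant is that of detection). Earlier in the same paragraph the plan says that "this sample size is sufficient to detect any real and important benefit of CBE over literacy training".
- **Loss:** the following paragraph says that "minimal loss to follow-up is expected, but we will impute assuming random missing-ness if needed". It adds that the mixed model keeps people who miss one follow-up survey. No loss rate is given.

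**The concern.** The calculation supports one point on a power curve: about 80% at 0.44. The restatement replaces that point with a range that has an upper limit (one behavior) but no lower limit, and the general sufficiency claim has no numerical anchor because no smallest important difference is named. Power falls steeply below 0.44, so the literal claim is wider than the calculation.

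The 0.44 also cannot be checked without knowing which test it belongs to. The contrast that the paragraph describes, tested two-sided, does not give it. At stake is the accuracy of the sample justification for the primary question: a reader should be able to see which advantages the trial has a good chance of detecting and which it does not.

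**Working it through.** **Inputs (all from Participants):** n = 100 per group, variance 4, correlation 0.80, power 80% (z = 0.842), p < .05 (z = 1.645 one-sided, 1.960 two-sided). Participants are treated as independent, and equal correlation between surveys is assumed for the average of both follow-ups.

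**Formulas:** SE = sqrt(2 × Var / 100). Detectable difference = (z_alpha + 0.842) × SE. Power at d = Φ(d/SE − z_alpha).

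**Step 1: reproduce 0.44.**

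*Baseline-to-6-month change.* Var = 2 × 4 × (1 − 0.8) = 1.6, so SE = sqrt(2 × 1.6/100) = 0.179.
- One-sided: 2.486 × 0.1789 = 0.445, which matches. Power at 0.44 is 79%.
- Two-sided: 2.802 × 0.1789 = 0.501, which does not match. Power at 0.44 is Φ(2.460 − 1.960) = 69%, and 80% power at 0.44 would need 130 per group.

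*Average of both follow-ups minus baseline.* Var = 4 × (1 + 0.9 − 1.6) = 1.2, so SE = sqrt(2 × 1.2/100) = 0.155.
- Two-sided: 2.802 × 0.1549 = 0.434, which matches. Power at 0.44 is 81%.
- One-sided: 0.385, which does not match.

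*6-month count adjusted for baseline.* SD 1.2 gives 0.475 two-sided and 0.422 one-sided. Neither matches.

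**Step 2: power away from 0.44, all 200 analysed.**

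| True difference | Average of follow-ups, two-sided | 6-month change, one-sided | 6-month change, two-sided |
|---|---|---|---|
| 0.2 | 25% | 30% | 20% |
| 0.3 | 49% | 51% | 39% |
| 0.4 | 73% | 72% | 61% |
| 0.44 | 81% | 79% | 69% |
| 0.5 | 90% | 88% | 80% |
| 0.75 | over 99% | over 99% | 99% |

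**Step 3: loss at 6 months.** The plan gives no rate, so 10% and 20% are assumptions. In the mixed model, people lost at 6 months still contribute baseline and post-program data. Given those two surveys, the residual variance of the 6-month count is 4 × (1 − 2 × 0.64/1.8) = 1.156. With loss L:
- 6-month change: Var = 0.444 + 1.156/(1 − L), which is 1.6 at L = 0.
- Average of follow-ups: Var = 0.911 + 0.289/(1 − L), which is 1.2 at L = 0.

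| Loss | Average of follow-ups, two-sided | 6-month change, one-sided | 6-month change, two-sided |
|---|---|---|---|
| 0% | 0.434 | 0.445 | 0.501 |
| 10% | 0.440 | 0.462 | 0.521 |
| 20% | 0.447 | 0.483 | 0.545 |

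For example, for the two-sided 6-month change at 20% loss: Var = 0.444 + 1.444 = 1.889, SE = sqrt(2 × 1.889/100) = 0.194, and 2.802 × 0.1944 = 0.545.

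**The case against.** The restatement follows directly on the 0.44 and is introduced as an explanation of it. It can fairly be read as a loose gloss: 0.44 is less than one, and the preceding sentence already presents 0.44 as the lower limit. On that reading it is right from about 0.44 to 1. This part of the objection stands. A reader might infer that the plan assigns 80% power to every advantage below one behavior, but the text does not say so. What remains is that the words set no lower limit of their own and, taken literally, cover values where power is half or less.

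Other stronger readings are also tempting and not supported:

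- **That the plan tests one-sided.** Sidedness is simply not stated. A two-sided test on both follow-ups also reproduces the figure, and Data analysis does use all three surveys.
- **That loss is ignored.** Minimal loss is expected on the strength of pilot engagement, retention measures are listed, and partial responders stay in the model. Dividing the sample by the fraction retained would overstate the effect because it discards their post-program data.
- **That the plan says a null result would rule out a very small benefit.** It makes no such statement. What a null result excludes depends on the confidence interval, whose 95% half-width with all 200 analysed would be about 0.30-0.35 (1.96 × 0.155 or 0.179). An estimate of zero would then exclude an advantage of 0.44.
- **That 0.44 is not small.** It is 22-44% of the expected baseline of 1-2 behaviors, but the checklist runs from 0 to 20 and no smallest important difference is named. The label is a matter of judgement, not a contradiction.

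**Conclusion.** The point holds as a correction to the power statement. The 0.44 is reproducible, but only for a contrast and sidedness that the text does not identify, and only with complete data. If the intended test is the two-sided baseline-to-6-month change, the detectable difference is 0.50 and power at 0.44 is 69%. Whichever of the three versions applies, power is at most about 51% at 0.3 and 30% at 0.2, so high probability is not supported below 0.44. The claim that any real and important benefit is detectable cannot be derived from the calculation. Attrition is a minor part: 10-20% loss adds roughly 0.01-0.04 behaviors to the detectable difference, depending on the contrast and sidedness.

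These figures rest on the plan's own variance and correlation, its linear approximation to the count outcome, independent participants, and equal correlation between surveys for the averaged contrast and the loss figures. The loss rates are assumptions. Nothing here shows that the trial is too small or that the analysis is wrong.

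**What to change.** In Participants:

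1. State the contrast (baseline to 6 months, or the average of both follow-ups) and the sidedness behind the detectable difference, and correct the figure to 0.50 if the test is the two-sided 6-month change.
2. Say that 80% power applies at that difference and above, and give power at 0.2, 0.3 and 0.4 behaviors.
3. State an assumed loss rate and the resulting mixed-model detectable difference: about 0.44-0.48 at 10-20% loss at 6 months in the reproducing cases, or 0.52-0.55 for the two-sided 6-month change.
4. Delete the description of the detectable advantage as very small and under one behavior, and the claim of sufficiency for any real and important benefit.

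The cost is wording and a slightly less favourable stated figure. Sample size and analysis do not change.
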